### Outcomes

The primary outcome of this trial is 6MWD measured at 16 weeks. Six-minute walk distance reflects peak oxygen consumption [22] in PAH and is associated with changes in HRQoL [23], with a minimal important difference (MID) of 33 m for PAH and 24 m for SSc-PAH [23]. The 16-week timepoint was chosen since nearly every proprietary drug for PAH has been approved based on changes in 6MWD at 3–4 months as this is considered a clinically important intermediate endpoint [17, 24–27]. Second, improvement in 6MWD in SSc-PAH patients can be seen in as few as 8 weeks in treatment-naïve patients [28]. We are following patients for one year and collecting 6MWD along with other data to assess the durability of the effect of sildenafil in SSc-MEP.

Secondary endpoints include change in pulmonary arterial compliance (PAC) and RV function by cardiac magnetic resonance imaging (CMR) and echocardiography, serum N-terminal probrain natriuretic peptide (NT-proBNP), and HRQoL at 16 weeks. Six-minute walk distance, NT-proBNP, HRQoL, and echocardiography are also obtained at 52 weeks. PAC is a measure of pulmonary arterial stiffness and a contributor to RV afterload which, due to the inverse hyperbolic relationship of PVR and PAC [29], may be modifiable early in the course of PAH. This is of significant relevance in SSc-PAH, since PAC is an independent predictor of survival [30]. Echocardiographic measures of RV function include tricuspid annular planar systolic excursion (TAPSE) [31] and speckle tracking echocardiography (STE), a quantitative measurement of regional and global contractility that is responsive to PAH treatment and correlates strongly with functional capacity and hemodynamics [32]. CMR, the gold standard for RV function assessment, is being employed to quantify RV ejection fraction and RV volumes. HRQoL is assessed using the Medical Outcomes Survey Short Form-36 (SF-36) [33] and emPHasis-10, a disease-specific tool developed specifically for PAH [34]. Testing protocols were standardized between the two enrolling sites; RHC, echocardiography, and CMR done at LSU will be interpreted centrally at Johns Hopkins.

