### Statistical methods

#### Sample size

We have based our effect size estimate of 45 m upon our preliminary data (not shown) demonstrating a difference in mean 6MWD between SSc patients with normal mPAP and SSc-MEP of ∼ 50 m with a standard deviation of 75 m. As such, we will have > 80% power to detect this difference at significance level of 0.05 with 27 subjects. To account for a 10% drop-out rate, we are enrolling 30 subjects. Even if our actual drop-out rate nearly doubles our expected rate (17% vs. 10%), we maintain adequate power to detect a difference of 45 m with 80% power (Fig. 3). While this estimate of change in 6MWD exceeds the MID for the 6MWD in PAH, the MID for this test in SSc-MEP is unknown. Further, if differences in 6MWD observed in the study do not reach the predefined detectable alternative, clinical relevance of the effect on 6MWD may be reflected by comparing the proportion of patients who exceeded the MID for 6MWD between arms. Based upon a sample size of 27 subjects completing the trial, we also have adequate power (80% or greater) to detect differences in the proposed secondary outcome measures. For instance, we have 80% power to detect a mean difference in PAC of 0.6 mL/mmHg (SD 1.1) between treatment arms; this difference was the average difference between these SSc-MEP and SSc-normal pressures found in our preliminary studies (data not shown). Further, we will have sufficient power to detect differences of 0.23 cm (SD 0.5) in TAPSE between groups which is close to the estimated MID for TAPSE in SSc-PAH (0.22 cm) from prior work from our group [28]. For global RV strain measured by STE, we have more than 85% power to detect a difference of 4.8% (SD 8%); this is the difference detected in our ATPAHSS Study of ambrisentan and tadalafil in treatment naïve SSc-PAH patients after therapy [28, 32]. Similarly, we have adequate power to detect a difference of 5% (SD 9%) in RVEF between arms; this difference is the MID for RVEF in PAH [35]. For HRQoL outcomes, we also have adequate power to detect clinically relevant changes in SF-36 of 5 units (SD 7 units) and emPHasis-10 of 6 units (SD 10) [36].

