#### Data analysis plan

The intent-to-treat analysis will include all randomized subjects. Hypothesis testing will use two-sided α = 0.05 without correction for multiplicity. We will characterize subjects regarding baseline and follow-up 6MWD and other endpoints. We will summarize demographics and other predictors of clinical status. Continuous variables will be summarized by the mean, median, standard deviation, and range, as appropriate. The distribution of the outcome measures of interest will be assessed for normality. If the distribution is normal, we will use independent t-tests to compare by treatment assignment. If the distribution is not normal, we will transform the data to meet the assumption of normality. If transformation does not achieve normality, comparisons between groups will be made using the Wilcoxon rank-sum test. We will use contingency tables for discrete and dichotomous variables.

The primary analysis will compare the absolute change in 6MWD from baseline with adjustment for baseline 6MWD, age, and sex in linear regression models. We chose sex as a potential confounder of the relationship between 6WMD and treatment based upon prior work demonstrating there may be worse survival for men with SSc-PAH compared to women [37], but men may have improved 6MWD and HRQoL compared to women in response to PDE-5 inhibitors [38]. Given the small sample size of our study, we will be sensitive to overfitting our model with covariates but will use the univariate analyses to inform the inclusion of additional covariates in the final model. We will examine the clinical relevance of the change in 6MWD by comparing the proportion of patients who achieve the MID for the 6MWD for both PAH (MID = 33 m) and for SSc-PAH (MID = 24 m) by treatment assignment. Using separate multivariable logistic regression models adjusting for baseline walk distance, age, and sex, we will assess if the odds of achieving a clinically relevant improvement in 6MWD based upon the MID for PAH and for SSc-PAH differs by treatment assignment. We can then perform responder analyses to determine characteristics of SSc-MEP patients likely to achieve either MID for the primary outcome of 6MWD.

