The secondary outcomes will be analyzed similarly using linear regression models adjusting for baseline values and for sex. Prior studies have demonstrated sex-specific differences in RV structure and function as assessed by CMR [39] and in PAC [29], though to our knowledge there are no studies examining differences in TAPSE between men and women. HRQoL measures may differ by sex as well.

We will also include longitudinal models of change from baseline over the time of the trial. Exploratory multivariate analyses will be performed incorporating all the available endpoint assessments (baseline, 4 months, and 12 months) in an ANCOVA model with active treatment/placebo status as the independent variable.

We will attempt to minimize missing data by encouraging full subject participation and follow-up even if the subject stops the study drug prematurely. If there are missing data, we will perform sensitivity analyses using the mean value obtained to replace this missing data. For subjects lost to follow-up, we will use all the information available until the end of follow-up. For dropouts, we will use the lowest value obtained to replace missing data in separate sensitivity analyses.

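### The two single-value substitutions planned as missing-data sensitivity analyses are not valid robustness checks, and the lowest-value rule can favour dropouts on endpoints where lower is better

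*Protocol article*

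**What the plan says.** All statements below are in the protocol article, under Data analysis plan unless noted.

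- Analysis set: "The intent-to-treat analysis will include all randomized subjects".
- Missing data in general: "we will perform sensitivity analyses using the mean value obtained to replace this missing data".
- Dropouts: "For dropouts, we will use the lowest value obtained to replace missing data in separate sensitivity analyses".
- Loss to follow-up: "For subjects lost to follow-up, we will use all the information available until the end of follow-up".
- Testing: "Hypothesis testing will use two-sided α = 0.05 without correction for multiplicity".

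Neither substitution says over whom the value is taken (all subjects, one arm, or the subject's own record) or whether it is a raw value or a change. Neither is limited to particular endpoints. The same section plans longitudinal models over baseline, 4 and 12 months. It also asks for continued follow-up after study drug is stopped, as does the section on data collection and participant timeline.

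The rules also matter after week 16, since Outcomes states: "Six-minute walk distance, NT-proBNP, HRQoL, and echocardiography are also obtained at 52 weeks".

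**The concern.** Substituting the lowest value is normally meant to be harsh on dropouts. It is harsh only where low is bad. The secondary outcomes run in both directions: higher is taken as better for PAC, TAPSE, RVEF and SF-36, and lower as better for emPHasis-10 and NT-proBNP. On the latter two a rule meant to penalise dropout would reward it, and dropout on active drug could look like benefit.

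Mean substitution has a different weakness. It fills gaps with values that carry no information, and what this does to the estimate and its standard error depends on which mean is used.

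At stake is the reader's ability to tell whether the result survives dropout. In a trial of 30 meant to inform a phase 3 study, that check will carry weight. Dropout may also be informative at week 52, because the Interventions section describes withdrawal from the trial on a week-16 hemodynamic finding. Such subjects could be given an average value or, on emPHasis-10 and NT-proBNP, the best one.

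**Working it through.** **Number of values to fill.** From Sample size: 27 completers and 10% dropout give 27/0.9 = 30 enrolled, which reproduces the plan's figure, so about 3 are missing. At the plan's 17%, 30 × 0.83 = 24.9, so about 25 complete and 5 are missing. Allocation is 1:1, so 15 per arm.

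**Other inputs.** For 6MWD, "We have based our effect size estimate of 45 m upon our preliminary data" and "with a standard deviation of 75 m". For emPHasis-10, 6 units with SD 10. Assumed: values missing at random; lower is better on emPHasis-10 and NT-proBNP; for the covariate-adjusted runs, baseline correlation 0.7 (6MWD) and 0.5 (emPHasis-10). Splits are written active:placebo.

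**Lowest value across subjects, no true effect.** With *a* and *b* dropouts in the two arms, the false difference is about (a − b)/15 × SD × k. Here k is the expected distance, in SDs, of the lowest of the observed values below their mean: 2.00 for 27 normal values, 1.97 for 25.

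| Split | emPHasis-10 (SD 10) | 6MWD, raw value (SD 75) |
|---|---|---|
| 3:0 | 3/15 × 10 × 2.00 = 4.0 | 3/15 × 75 × 2.00 = 30 m |
| 4:1 | 3/15 × 10 × 1.97 = 3.9 | 3/15 × 75 × 1.97 = 29.6 m |
| 2:1 | 1/15 × 10 × 2.00 = 1.3 | 1/15 × 75 × 2.00 = 10 m |

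On emPHasis-10 the difference favours the arm with more dropouts, and 3.9/6 = 65% of the target. On 6MWD it goes against that arm. Simulation agrees: 4.0 units at 3:0 with type I error 12.6% (t-test), and about 4.0 at 4:1 and 1.4 at 2:1 with baseline adjustment. Applied to change in 6MWD rather than the raw value, the adjusted figures are about 23 m (4:1) and 8 m (2:1).

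**Lowest value across subjects, true effect present** (simulated t-test, 15 per arm):

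| Split | 6MWD, true 45 m | emPHasis-10, true −6 |
|---|---|---|
| 2:1 | 30.1 m | −6.8 |
| 3:2 | 27.1 m | −6.4 |
| 3:0 | 8.8 m | −9.5 |
| 0:3 | 71.2 m | −1.2 |

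So the 6MWD effect can shrink or grow. The reported standard error is too large: 31.9 against a true spread of 25.6 at 2:1, and 33.5 against 24.5 at 3:2. Type I error for 6MWD is 2.8% and 1.7% at those splits, but 12.5% to 12.8% when all three dropouts are in one arm, because the bias then dominates. Had emPHasis-10 dropouts received the worst score instead, a true −6 would become about −4.0 (2:1) or −1.2 (3:0).

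**Subject's own lowest.** A dropout before week 16 has only a baseline, so the change is baseline − baseline = 0. A dropout between weeks 16 and 52 gets the lower of two values, which on a lower-is-better endpoint means no change or an improvement. Neither is pessimistic.

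**Pooled mean.** With N observed in total and n_A, n_B observed per arm, the effect is multiplied by 1 − (a·n_B + b·n_A)/(15N).

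- 2:1: 1 − (2×14 + 1×13)/(15×27) = 1 − 41/405 = 0.899, so 45 m becomes 40.4 m.
- 3:2: 1 − (3×13 + 2×12)/(15×25) = 1 − 63/375 = 0.832, so 45 m becomes 37.4 m.

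The standard error falls with it. In the adjusted analysis at 3:2 it is 18.5 reported against 18.4 true, with type I error about 5%.

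**Arm mean.** The effect stays at 45 m. At 3:2 the adjusted standard error is about 18 reported against 22 true, with type I error about 10%. The unadjusted t-test gives 24.5 against 30.1 and 10.4%; at 2:1 it gives 25.6 against 28.8 and 7.8%.

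**The case against.** The strongest reply is that both rules are labelled sensitivity analyses, so the primary estimate does not depend on them. That stands, and it limits the harm to the robustness check.

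Second, the article condenses a fuller protocol that may define the reference set and direction. Those details alone would be no finding. But the article does more than leave them out: it states a lowest-value rule for dropouts with no endpoint exempted, and followed as written that rule misleads. The article also does not state the direction of emPHasis-10 or NT-proBNP, so that remains an assumption here.

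Third, the large figures need lopsided dropout. That also stands: at the planned 10% with a 2:1 split, the shift under no effect is about 8 to 10 m or 1.4 units.

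Three stronger readings are tempting and not supported:

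- A reader might infer that mean substitution always understates the error. It does so with an arm mean, not with a pooled mean. Shrinkage and understated error belong to different readings of the rule.
- A reader might infer that these substitutions are the plan's only answer to missing data. The same section uses available data for subjects lost to follow-up, plans longitudinal models and continues assessments after treatment stops.
- A reader might infer that the rules generally move the result by most of the design effect. That requires dropouts concentrated in one arm.

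**Conclusion.** The concern holds in a limited form. Both substitutions are unsuitable as robustness checks, and neither alters the primary estimate.

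The clearest fault is direction. Taken across subjects, the lowest-value rule rewards dropout on emPHasis-10 and NT-proBNP, by about 4 emPHasis-10 units under a 3:0 or 4:1 split and about 1.4 under 2:1. On 6MWD its answer depends mainly on which arm loses subjects. Taken within subject, it is not pessimistic before week 16. The mean rule either shrinks the effect by 10% (three missing) to 17% (five missing) with valid type I error, or leaves the effect alone and raises type I error to about 8% to 10%.

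These sizes assume missingness at random, normal outcomes and the stated SDs; the adjusted figures also assume the baseline correlations given above. The pooled-mean shrinkage factor does not depend on the SD. The change is worth making before unblinding, because it is cheap and the check will be read as evidence of robustness.

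**What to change.** Replace both substitutions with one of the following:

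- multiple imputation by arm, using baseline, age, sex and center; or
- a likelihood-based repeated-measures model that keeps baseline as an outcome, so that a subject with only a baseline still contributes. A model of change from baseline would not achieve this for dropouts before week 16.

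Add a delta-adjusted (tipping-point) sensitivity analysis with the penalty set toward worse for each endpoint. List the worse direction of every endpoint beforehand, including the sign convention for RV strain.

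At minimum, change lowest to worst in that endpoint's direction, state the reference set and whether it applies to the raw value or the change, and delete mean substitution.

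The cost is a wording change and modest programming. No new data, visits or subjects are needed.

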### Data monitoring

The Data Safety and Monitoring Board (DSMB) will be comprised of three members: two pulmonary hypertension specialists with extensive track records of participating in and leading randomized controlled trials in PH, as well as one biostatistician experienced in clinical trial analysis. DSMB reports will be generated on a quarterly basis including expected and actual enrollment numbers. Every six months, a DSMB report will be generated that includes enrollment rates, follow-up rates, compliance levels, adverse events, mortality, and mean data on the primary and secondary analysis. If there are any complaints about the research trial, we will summarize these complaints and report them to the DSMB in these reports. Since this is a Phase II trial that would be helpful in supporting future studies of the intervention even if no difference is found between sildenafil and placebo, we have not planned for formal interim analyses for futility.

### Ethics approval and consent to participate

The study is being conducted in compliance with the principles of Declaration of Helsinki and informed consent is obtained from all the participants. For each consent process, study personnel discuss the details of the study, the risks and benefits, and the subject’s rights and responsibilities if they choose to participate in the trial and their right to refuse to participate. It is made clear that their clinical care will not be affected by their decision. Subjects are permitted to provide verbal consent over the phone prior to being scheduled for a screening visit. A consent script is provided, and documentation of verbal consent is noted. When the subject arrives for the screening visit, written consent is obtained.

Johns Hopkins University and Louisiana State University Health Sciences Center are relying on a single IRB (sIRB) of record (JHU) and obtain approval and reliance agreements. IRB approval was required at both enrolling sites prior to enrollment of the first patient. Protocol changes must be approved by the sIRB prior to implementation. Unanticipated problems posing risks to subjects or others will be reported to the sIRB. Reportable events include any event that could represent an unexpected serious adverse event (SAE), any AE that could lead to a change in the informed consent, information that changes the risks and benefits of the trial, a change in FDA labeling for sildenafil, breach of confidentiality, protocol violations that might place one or more participants at increased risk or might affect the rights of the subjects.

### Data management, sharing, and dissemination

Confidentiality is maintained by assigning each participant with a unique study number; no Protected Health Information (PHI) is recorded on study case report forms (CRF) or transmitted between study sites. We keep any potential identifiers separate from the participant’s CRF in a secure environment only accessible to study staff granted access to PHI. Only study staff approved by the IRB have access to study records, data, and specimens. Representatives from the funding organization, the Department of Defense, are eligible to review study records.

Clinical site personnel key in all study data into the data capture system directly. Other than the two questionnaires, study data is entered directly from the electronic medical record, rather than by use of paper CRF’s. The electronic data capture system that we are using is REDCap (https://www.project-redcap.org/), which is a secure, validated web application used by both Johns Hopkins and Louisiana State University Health Sciences Center to build and manage databases. The paper forms (questionnaires) are kept in locked offices only accessible by approved study staff. To ensure data quality, all data is double-entered (enter/verify). A second method of quality control is embedded within REDCap, which provides data checks in real time as data are keyed, including data format checks (e.g., numbers or letters) and valid value checks (e.g., ranges for age). The site Principal Investigator (PI) performs continuous monitoring of data quality and completion of CRFs. Once the site personnel mark a form as complete, the data on that form is locked and all error corrections must be requested. Each time an error correction is done after the data form is locked, a rationale must be provided. Data will be exported only in de-identified custom exports and only by approval of the PI.

Results of this clinical trial will be disseminated to the research community through presentations at national/international conferences as well as through publications in peer-reviewed journals. Data collected during this clinical trial will be shared, both in aggregate through manuscripts and individual-level (de-identified) data upon request. The data will be encoded using standard methods and a coding key will be available to interested researchers. Additionally, biospecimens may be available for sharing if adequate samples remain after our analyses are complete. In this case, a Materials Transfer Agreement would be required according to institutional policy. Data will be distributed directly to interested researchers by request via an electronic file. Data may also be submitted to the NHLBI-funded Biologic Specimen and Data Repository Information Coordinating Center (BioLINCC), as the biomarker portion of our trial aligns with their mission.

## Discussion

To our knowledge, once completed the SEPVADIS trial will be the first RCT to exclusively enroll patients with mildly elevated mean pulmonary artery pressure (21-24mmHg). Since the recommended definition of PH changed in 2018, there has been great uncertainty about whether PAH-specific medications are beneficial in this new subgroup of patients, especially in a high-risk group such as SSc. The SEPVADIS trial is currently enrolling patients at both clinical sites and once completed will provide important data on the impact of sildenafil on exercise capacity, right heart function, and HRQoL in SSc patients with mildly elevated pulmonary artery pressure. We anticipate that these data will lay the foundation for a larger, multi-center trial of PAH-specific medications in SSc-MEP, which has the potential to slow progression of disease and positively impact patient outcomes.

## Data Availability

N/A.

## Abbreviations

6MWD: six-minute walk distance
6MWT: six-minute walk test
ACR: American College of Rheumatology
ANCOVA: analysis of covariance
BP: blood pressure
CI: Cardiac index
CMR: cardiac magnetic resonance imaging
CRF: case report form
CTA: chest CT angiography
DSMB: Data Safety and Monitoring Board
ERA: endothelin receptor antagonist
EULAR: European League Against Rheumatism
FC: functional class
FDA: Food and Drug Administration
HRCT: high resolution computed tomography
HRQoL: health-related quality of life
ILD: interstitial lung disease
JHU: Johns Hopkins University
LVEF: left ventricular ejection fraction
m: meter(s)
mmHg: millimeters of mercury
MEP: mildly elevated pulmonary pressure
MID: minimal important difference
mPAP: mean pulmonary artery pressure
NHLBI: National Heart, Lung, and Blood Institute
NT-proBNP: N-terminal B-type natriuretic peptide
PAC: pulmonary artery compliance
PAH: pulmonary artery hypertension
PAWP: pulmonary artery wedge pressure
PDE-5: phosphodiesterase-5
PH: pulmonary hypertension
PHI: Protected Health Information
PI: Principal Investigator
PVR: pulmonary vascular resistance
RCT: randomized controlled trial
RHC: right heart catheterization
RV: right ventricle
SAE: serious adverse events
SD: standard deviation
SEPVADIS: **S**ildenafil versus placebo for **e**arly **p**ulmonary **v**ascular **d**isease **i**n **s**cleroderma
SF-36: Short Form 36 questionnaire
sIRB: single institutional review board
SSc: systemic sclerosis
STE: speckle tracking echocardiography
TAPSE: tricuspid annular planar systolic excursion
VQ: ventilation-perfusion scan
WHO: World Health Organization
WSPH: World Symposium on Pulmonary Hypertension
